### Interim analyses {21b}

The data monitoring committee will conduct monthly analyses to ensure that there are no significant harms related to participating in this project. The members of the data monitoring committee will all have access to these interim analyses. Termination of the trial will be decided in unison, but in case of disagreement, the final decision lies with the primary investigator.

### Methods for additional analyses (e.g., subgroup analyses) {20b}

A large number of additional analyses will be conducted. Logistic regression will be used to analyze associations between treatment arms and the secondary outcome YODA (dichotomized) at 3-month follow-up post treatment as well as each of the 20 NEQ items at post-treatment. Linear mixed model regression will be used to analyze associations between treatment arms and the following outcomes through all time points from pre-treatment to 12-month follow-up post treatment: SCAS-C score, CALIS, MFQ score by adolescent, SCAS-P, CALIS, MFQ score by parent, EQ-5D-5L score, CSQ-8 score, and SUS score. Furthermore, linear mixed model regression will be used to analyze associations between treatment arms and WAI-SF at treatment sessions 2, 4, 6, 8, and 10 and at post treatment, and between treatment arms and weekly measures of CAS-8 and S-MFQ. Linear regression will be used to analyze associations between treatment arms and WAI-TECH-SF and engagement at post-treatment, as well as the cost-effectiveness analysis.

Finally, we wish to conduct a post hoc exploratory growth mixture model that can provide trajectories of change in symptoms through the trial across the different sessions and post-measurements.

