**Methods:**

The study is structured as a parallel three-armed randomized controlled trial, comparing Internet-delivered Cognitive Behavioral Therapy (iCBT) with planned feedback, iCBT with on-demand feedback, and a waitlist control group, each group including 56 participants. Participants in the two iCBT conditions will undergo a 14-week treatment regimen, while those in the waitlist control group will wait for 14 weeks before starting iCBT with planned feedback. Additionally, participants in the iCBT groups will be randomly assigned to receive a booster session or not. The study design is factorial including two factors: type of therapist feedback (factor 1) and booster or no booster (factor 2). The study population comprises adolescents aged between 12 and 17 years, residing in Denmark, diagnosed with an anxiety disorder according to DSM-5 criteria. The primary outcome measures are the Youth Online Diagnostic Assessment and the Spence Children’s Anxiety Scale. Assessments will occur at baseline, post-treatment, and at 3-, 6-, and 12-month follow-ups post-treatment.

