### Trial design {8}

The study is a randomized controlled trial (RCT) designed as a superiority trial with three parallel conditions: (1) iCBT with planned feedback, (2) iCBT with on-demand feedback and (3) waitlist control. The allocation ratio is 1:1:1 for each condition. The participants will be stratified by age into age groups 12–14 years and 15–17 years respectively to secure an even age distribution across conditions. Additionally, all active participants will be randomized to receive a booster session 10 weeks after end of treatment. The randomization will take part 10 weeks into treatment with an allocation ratio of 1:1. The design of the randomized trial is thus factorial including two factors: type of therapist feedback (factor 1) and booster or no booster (factor 2). Data will be collected using parent and adolescent questionnaires at five time points: pre-treatment, post-treatment and at follow-ups after 3, 6 and 12 months post-treatment. Participants in the waitlist condition will no longer take part in the study after the post waitlist measures, but will be offered iCBT with planned feedback after completing the waitlist period (Fig. 1).

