Other secondary outcomes include outcomes related to overall participant experience, they are therefore not administered at pre-treatment. This includes participant satisfaction with treatment and with system usability, measured by Working Alliance Inventory applied to Internet (WAI-TECH-SF) [54]. WAI-TECH-SF assesses the technical alliance. The WAI-TECH-SF has shown good psychometric properties and excellent internal consistency [54].

Working Alliance Inventory – Short Form (WAI-SF) [55]. The therapeutic alliance will be assessed using the short version of the Working Alliance Inventory. The WAI-SF is a 12-item self-report questionnaire designed to assess the therapeutic alliance with the therapist / online program in a self-guided intervention on three dimensions: therapeutic goals, tasks, and bonds. The WAI-SF will be administered after week 2, 4, 6, 8 and 10 and at post-treatment and be completed by both adolescents and parents.

Client Satisfaction Questionnaire-8 (CSQ-8) [56] is used to measure general satisfaction with the received treatment. The scale has shown high internal consistency and concurrent validity [57].

System Usability scale (SUS) [58] is used to assess the subjective experience of usability of a computer system. A Danish version of the SUS has been validated in a mental health care setting [59].

Negative Effect Questionnaire (NEQ) [60] is a 20-item questionnaire used to monitor the occurrence of negative effects in psychological treatments. NEQ shows acceptable psychometric properties [60].

Engagement with the treatment program will be measured objectively using the number of logins to the treatment program as well as number of words per message sent to the therapist and number of words per text box in the modules. These data are automatically logged in the treatment platform and will be registered for both adolescents and parents.

Completion of the treatment program is defined as completing module 8 for adolescents or being active in the treatment program for all 14 weeks.

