### Sample size {14}

The sample size calculation is based on scenarios of difference between treatment and waitlist at end of treatment for the primary outcome SCAS, based on Stjerneklar and colleagues [32] previous study detecting a difference of 10 points between the waiting list and the (combined) treatment groups in change in SCAS score from baseline to 3 months’ follow-up. Using a linear mixed model with outcome variance *σ*^2^=225 (*σ* = 15) and intraclass coefficient ICC=0.6 [32], and with significance level *a* = 0.05 and power = 1−b = 0.80, allowing for unequal group sample sizes (randomized 1:2), a total sample size of 134 patients is needed [64, 65]. Allowing for 20% attrition, a total of *n* = 168 patients (*n* = 56 waiting list, *n* = 112 treatment) will be included.

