## Statistical methods

### Statistical methods for primary and secondary outcomes {20a}

The primary analysis are the association between the change in SCAS-C/P total score from pre- to post-treatment and trial condition will be analyzed using linear mixed model regression.

For the secondary analysis, the association between YODA, dichotomized as YODA total score ≥ 1 vs. YODA total score < 1, and the three trial conditions at post-treatment will be analyzed using logistic regression.

A more detailed analysis plan will be developed prior to the end of recruitment for both primary and secondary analyses in collaboration with a statistician employed at the participating organizations.

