### Adverse event reporting and harms {22}

Another committee, comprising clinicians working on the project and members of the research team, will be established to monitor individual risks on a case-to-case basis. This committee will oversee screening for depression and suicidality using S-MFQ scores, and anxiety symptom severity using CAS-8. Screening will occur daily, with exceptions for holidays and weekends.

Additional negative effects will be assessed through the NEQ after the adolescent have completed 14 weeks of treatment. If any risks or harms are detected, the committee will report to the assigned clinician. It will then be the clinician’s responsibility to contact the participant, and/or their legal guardians to investigate if the participant needs additional help. All adverse events will be recorded in the trials database.

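### The dedicated negative-effects questionnaire (NEQ) is analysed only as 20 separate item regressions, with no summary measure; a minor point, but cheap to improve

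*Protocol article*

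**What the plan says.** In the Protocol article, Secondary outcomes introduces the NEQ, which "is a 20-item questionnaire used to monitor the occurrence of negative effects in psychological treatments". Adverse event reporting and harms {22} gives its timing: "Additional negative effects will be assessed through the NEQ after the adolescent have completed 14 weeks of treatment".

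The analysis is in Methods for additional analyses {20b}, which opens with "A large number of additional analyses will be conducted". It then assigns logistic regression on treatment arm to the YODA at 3 months "as well as each of the 20 NEQ items at post-treatment". No NEQ total, count or other summary appears in that section or elsewhere in the article. Within {20b}, only the growth mixture model is called exploratory.

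The only significance level in the article belongs to the SCAS sample size: "with significance level *a* = 0.05 and power". Section {20a} defers detail: "A more detailed analysis plan will be developed prior to the end of recruitment for both primary and secondary analyses".

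**The concern.** The NEQ is the one instrument chosen specifically to capture negative effects of treatment, yet the only stated way of comparing arms on it is item by item. Twenty tests in arms of about 50 adolescents can go wrong in two directions. One or more items may differ by chance and be reported as a harm of one feedback format. And any single item has limited power, so a real but spread-out excess of negative effects may go unseen because nothing pools the items. Rare items add a third difficulty, since ordinary logistic regression breaks down when an arm has no events.

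**Working it through.** **Inputs from the article.** Methods in the abstract gives "each group including 56 participants"; Trial design {8} says "The allocation ratio is 1:1:1 for each condition". Sample size {14} allows 20% attrition on 134 evaluable participants: 134 / 0.80 = 167.5, so 168, and 168 / 3 = 56 per arm. With 20% loss, 56 × 0.80 = 44.8, about 45 per arm. The article gives no error rate, power or item prevalence for the NEQ, so there is no NEQ figure to reproduce.

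**Assumptions.** Two-sided 0.05 for each item; one contrast per item, planned versus on-demand feedback (inferred from the NEQ's timing, as the assessment schedule is not shown); item prevalences as stated below.

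**1. Chance of at least one false positive among 20 items.**
- Independent tests: 1 − 0.95^20 = 0.64, with 20 × 0.05 = 1.0 false positive expected.
- Equicorrelated test statistics (simulation): 0.59 at correlation 0.2, 0.54 at 0.3, 0.42 at 0.5, 0.29 at 0.7.
- Participant-level simulation, 45 per arm, item prevalences spread over 5-40%, latent correlation 0 to 0.7: about 38-54% with Wald tests, and up to about 68% with likelihood-ratio tests.
- All items at one prevalence, 45 per arm, latent correlation 0 to 0.5:

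| Prevalence | Wald | Likelihood ratio |
|---|---|---|
| 5% | about 0.02 | 0.81-0.85 |
| 10% | 0.27-0.31 | 0.65-0.71 |
| 20% | 0.52-0.59 | 0.58-0.67 |
| 30% | 0.53-0.63 | 0.55-0.67 |

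For rare items the answer therefore depends on which test is used. At 5% prevalence the likelihood-ratio test rejects 9% of the time per item under no difference, and the Wald test 0.1%.

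If the waitlist arm also completed the NEQ and 2 or 3 contrasts were tested per item, 40 or 60 tests would give 1 − 0.95^40 = 0.87 or 1 − 0.95^60 = 0.95. These are upper guides, because the contrasts share arms.

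**2. Power for one item at 0.05.** For 10% versus 20% with n = 45 per arm, the normal approximation is

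Φ{[0.10 − 1.96 × √(2 × 0.15 × 0.85 / 45)] / √[(0.10 × 0.90 + 0.20 × 0.80) / 45]} = Φ{(0.100 − 0.1475) / 0.0745} = Φ(−0.64) = 0.26.

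Exact binomial enumeration gives 0.22 (Wald) and 0.28 (likelihood ratio). Other cases, by normal approximation:

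| Item rates | 45 per arm | 56 per arm |
|---|---|---|
| 5% vs 15% | 0.35 | 0.42 |
| 10% vs 20% | 0.26 | 0.32 |
| 20% vs 30% | 0.19 | 0.23 |
| 20% vs 40% | 0.55 | 0.64 |
| 5% vs 25% | 0.77 | 0.85 |

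**3. Empty arms.** At 5% prevalence, P(no events in one arm of 45) = 0.95^45 = 0.099. At least one empty arm: 1 − (1 − 0.099)² = 0.19.

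**4. What a summary would do.** A rank comparison of the number of items endorsed (20 items, prevalences 5-40%, 45 per arm) has simulated size of about 5%. With an odds ratio of 2 on every item, its power is about 0.57-0.88 over latent correlations from 0.7 down to 0.3. Bonferroni over 20 items (0.05 / 20 = 0.0025 each) would also control error, but it cuts power for 10% versus 20% at 45 per arm from 0.26 to 0.04.

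**The case against.** A reader might infer that the plan tests all 20 items at full alpha. The article does not say so. It states no alpha, sidedness, multiplicity rule or decision rule for these tests. The NEQ is a secondary outcome, so it falls within the detail that {20a} defers to an analysis plan that is not shown. Multiplicity rules, exploratory labels and sparse-data estimators commonly sit there, and their absence from the article is not a fault.

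A reader might also infer that this is the only harms comparison between arms. It is not. Section {22} uses the S-MFQ and CAS-8 for risk screening, and {20b} compares arms on both, as well as on the MFQ. Interim analyses {21b} adds monthly harm reviews, and {22} records all adverse events.

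Nor does the document support saying that a doubling of an item will usually be missed. That holds for 10% versus 20%, but 20% versus 40% has about 55% power at 45 per arm. The chance of a false positive is not always high either: strong correlation lowers it to 0.29-0.42, and Wald tests on items at 5% bring it to about 0.02.

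Finally, screening harms item by item without adjustment is defensible, because adjustment costs power to detect harm, and a count adds unlike effects together. Each of these objections stands. None supplies a summary comparison: the method the article does state is 20 item regressions and nothing that pools them.

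**Conclusion.** The point holds as a minor, secondary-level improvement to a stated method. The NEQ is analysed only item by item. If the items are each tested at an unadjusted two-sided 0.05, the chance of at least one spurious difference is 64% under independence and roughly 38-68% under the mixed-prevalence simulations. A 10-point difference on one item (10% versus 20%) is found only about 22-28% of the time with 45 per arm, and at 5% prevalence about 19% of items have an arm with no events. The alpha, the single contrast and all item prevalences are assumptions; the article gives none of them for the NEQ. No success criterion, stopping rule or safety conclusion is tied to any single item, so the main results are not affected.

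**What to change.** In Methods for additional analyses {20b}, name one pre-specified NEQ comparison between the arms that complete the questionnaire: the number of negative effects endorsed per adolescent, reported with a 95% CI. Report all 20 items by arm as frequencies with descriptive effect estimates, labelled exploratory, and use Firth or exact logistic regression where events are sparse.

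The cost is a change of wording; no data or participants are added. Item-level p-values lose any inferential status. The count gains power only for differences spread over many items and is nearly blind to a difference confined to one, so the item table has to be kept alongside it. If the unseen analysis plan already does this, the article's sentence only needs to be brought into line with it.

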### Methods in analysis to handle protocol non-adherence and any statistical methods to handle missing data {20c}

Linear mixed models, which tolerate missing values and minimize the loss of statistical power in case of drop-out, will be fitted using the maximum-likelihood estimation method and based on the intention-to-treat sample. Where relevant in other types of analyses, missing data will be handled using multiple imputation methods.

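### Naming maximum likelihood for all linear mixed models makes standard errors slightly too small: about 1% in the primary contrast, about 2% in a four-cell booster model

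*Protocol article*

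**What the plan says.** Section {20c} of the protocol article states that linear mixed models "will be fitted using the maximum-likelihood estimation method", on the intention-to-treat sample. The reason given is that such models tolerate missing values and limit the loss of power from drop-out. No small-sample degrees of freedom and no reference distribution are named.

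The sentence covers the primary analysis in section {20a}, where the association between "change in SCAS-C/P total score from pre- to post-treatment and trial condition will be analyzed using linear mixed model regression". It also covers the mixed models in section {20b}, several of which run from pre-treatment to 12-month follow-up.

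Section {8} describes a factorial design in "type of therapist feedback (factor 1) and booster or no booster (factor 2"). It also says that the waitlist arm leaves the study after its post measures, so any later between-group contrast rests on the iCBT participants only.

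Section {20a} promises a more detailed analysis plan before recruitment ends.

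**The concern.** ML estimates variance components as if the fixed effects were known. The estimates are therefore biased downward, by an amount that depends on the number of fixed effects relative to the number of participants. Standard errors inherit the bias, always in the direction of intervals that are too narrow and p-values that are too small.

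REML removes this bias and uses the same incomplete records. The rationale in {20c}, tolerance of missing data, applies equally to REML and gives no reason to prefer ML.

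At stake is a small optimism in every mixed-model interval. It is greatest where many cell means are estimated from few participants, which here means a model with all four feedback-by-booster cells. The booster effect is one of the hypotheses stated in section {7}.

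**Working it through.** **Inputs from the protocol**
- Section {14}: "allowing for unequal group sample sizes (randomized 1:2), a total sample size of 134 patients is needed", and 20% attrition. Check: 134 / 0.8 = 167.5, rounded up to 168, split 56 and 112. This matches the stated total.
- iCBT participants after 20% attrition: 112 × 0.8 = 89.6, so 90.
- SD 15 and ICC 0.6, from section {14}. Only the simulation needs them; the closed form does not.

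**Assumptions**
- Two-sided 5% tests, a random intercept, and a separate mean for each group at each occasion.
- p is the number of groups in the model: 3 (arms), 2 (feedback arms) or 4 (feedback-by-booster cells).

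**Step 1. ML alone.** For a within-person contrast the ML variance is (n − p)/n of the unbiased one, so the ratio of ML to REML standard error is r = √((n − p)/n).
- Primary, n = 134, p = 3: √(131/134) = 0.989, or 1.1% too small.
- iCBT-only, two feedback arms, n = 90, p = 2: √(88/90) = 0.989, or 1.1% too small.
- iCBT-only, four cells, n = 90, p = 4: √(86/90) = 0.978, or 2.2% too small.

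**Step 2. Type I error from ML with a t reference on n − p degrees of freedom**, P(|t| > t₀.₉₇₅ × r).
- Primary: 5.26%, an excess of about 0.3 points.
- Two feedback arms: 5.26%, the same.
- Four cells: 5.53%, an excess of about 0.5 points.

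**Step 3. ML with a normal reference**, P(|t| > 1.96 × r). The protocol does not fix this choice; REML with the same normal reference is shown to separate the two causes.

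| Contrast | ML + normal | REML + normal | Due to ML | Total narrowing of interval |
|---|---|---|---|---|
| Primary, n = 134, p = 3 | 5.48% | 5.21% | 0.27 points | 2.0% |
| Two feedback arms, n = 90, p = 2 | 5.58% | 5.32% | 0.26 points | 2.5% |
| Four cells, n = 90, p = 4 | 5.87% | 5.32% | 0.55 points | 3.6% |

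Total narrowing is 1 − 1.96 × r / t₀.₉₇₅. For the primary contrast, 1.96 × 0.9887 / 1.9782 = 0.980. For four cells, 1.96 × 0.9775 / 1.9879 = 0.964.

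**Step 4. Five occasions.** The n − p degrees of freedom suit a two-occasion change. With five occasions and complete data, a random-intercept model has about 4 × (n − p) within-person degrees of freedom. For four cells that is 4 × 86 = 344, and ML with a normal reference gives 5.62% with 2.6% narrowing. Hence the 5.6–5.9% range for four cells.

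**Step 5. Simulation.** There were 3,000 replicates per scenario, with SD 15, ICC 0.6 and monotone drop-out of 20% from the full randomised numbers. ML and REML were fitted to the same data, with a normal reference.

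| Scenario | SE ratio ML/REML | Type I error, ML | Type I error, REML |
|---|---|---|---|
| Primary, 3 arms, 2 occasions | 0.989 (2.379 vs 2.404 points) | 5.5% | 5.3% |
| 2 feedback arms, 5 occasions | 0.990 | 5.9% | 5.7% |
| 4 cells, 5 occasions | 0.980 | 5.6% | 5.1% |

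The Monte Carlo standard error of each error rate is about √(0.055 × 0.945 / 3000) = 0.4 points. The standard error ratios are therefore the firmer result, and they agree with Step 1.

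**The case against.** The strongest case against has four parts.

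- **ML is a legitimate estimator at 134 to 168 participants.** This stands. The protocol contains no wrong number or contradiction here, and a 1% change in a standard error will not alter the primary conclusion.
- **The sentence sits under the missing-data heading and may only mean likelihood-based handling of drop-out, with details left to the analysis plan.** That may be the intention. As written, though, it names a specific estimator. The later plan must either carry ML forward or depart from the published text, so this is a stated choice and not just an absent detail.
- **Part of any narrowing depends on a normal reference, which the protocol never names.** This stands. A reader might infer that ML by itself makes intervals 2–4% too narrow. The documents do not support that: ML accounts for about 1% in the primary contrast and 2% in the four-cell model, and the rest appears only if normal-based tests are used.
- **Smaller samples at follow-up do not automatically make it worse.** This also stands. A reader might infer a larger ML effect in every iCBT-only contrast. A two-arm feedback contrast at n = 90 loses the same 1.1% as the primary, because p falls along with n. Only a four-cell model loses more, and section {20b} refers to treatment arms without specifying such a model.

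Larger figures can be produced by assuming attrition well above 20%. Section {14} plans for 20%, and although the Discussion warns of possibly high drop-out it gives no figure, so those results are not relied on.

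**Conclusion.** The point holds as a minor improvement. Naming ML makes standard errors about 1% too small in the primary contrast and in a two-arm feedback contrast, and about 2% too small in a four-cell feedback-by-booster model at 20% attrition. ML itself adds about 0.3 and 0.5 percentage points of type I error respectively. If normal-based tests are also used, the total is about 5.5% for the primary and 5.6–5.9% for four cells.

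This rests on a random-intercept model with group-by-occasion means, two-sided 5% tests and the sample sizes in section {14}. The four-cell figures also assume that the booster analysis fits all four cells. Nothing here threatens the primary conclusion.

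**What to change.** In section {20c}, or at the latest in the forthcoming analysis plan with the departure noted, replace the estimation wording with: *fitted by restricted maximum likelihood with Kenward-Roger or Satterthwaite degrees of freedom, on the intention-to-treat sample*. This removes the ML bias and also settles the reference distribution.

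The cost is one line of text and one software option. The incomplete records are used in the same way, point estimates are essentially unchanged and no further participants are needed. Intervals widen by about 1% (primary, if t-based tests were intended anyway: 1/0.989 = 1.011) to about 4% (four cells, if normal-based tests were intended: 1/0.964 = 1.037).
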